### Data analysis

Descriptive statistics will be used to summarize the socio-demographic characteristics and clinical data (as listed above) of all subjects at all time points. Generalized estimating equations (GEE) with unstructured working covariance matrix at the individual level with repeated measurements will be performed to compare all outcomes [1–5] between groups (i.e., time effect, group effect, group*time effect). An intention-to-treat principle will be adopted. Multiple imputations will be used to account for missing data, and reporting will follow the guideline published in *BMJ* [54]. Sensitivity analysis will be performed to compare the results between complete and non-complete cases. All demographic and clinical variables (e.g. age, gender, religiosity, expectation on treatment credibility, etc.) will be accounted for in the analysis. Both crude and adjusted GEE model analyses will be performed. All statistical tests will be two-tailed and statistical significance will be set at 0.025. IBM SPSS 25.0 will be used.

Path analysis will be used to examine the mediating role of biomarkers and level of mindfulness on the effect of mindfulness training on psychological distress. Based on the hypothesized mediation model (Fig. 2), a baseline path model will be first built, then a path model with the same structure for T1 will be added and linked by intra-correlations among the same variables. The mediation effects of biomarkers and level of mindfulness on the effect of mindfulness training on psychological distress will be assessed through the significance of the corresponding products of indirect path coefficients from mindfulness training to psychological distress, respectively [55]. In view of the possibility of violation of normality assumption, a bootstrapping approach, instead of the conventional multivariate delta method, will be used to estimate the standard errors and the confidence intervals of the product terms (mediation effects) [56]. The path analyses and the bootstrapping will be performed using IBM SPSS 25.0.

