## Methods

### Study design and setting

This is a multi-centre, assessor-blinded, 3-arm randomised waitlist-controlled trial with sequential mixed-method design to evaluate the effect and acceptability of 8-week programs using individual mindfulness techniques (yoga alone and meditation alone), compared to wait-list usual care control. Figure 1 shows the CONSORT flow diagram. Repeated outcome measures will be assessed at three time points across the 6-month study period to quantitatively evaluate the immediate and sustained effects of each mindfulness technique on anxiety and depression and other physio-psycho-spiritual outcomes in PD patients, compared with the usual care control group. Assessment time points are: baseline (Prior to randomization, T_0_), 8 weeks (T_1_: 1-week post-intervention), and 24 weeks (T_2_: 4-month post-intervention).

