### Outcome measures

To detect the intervention effects, the following instruments will be used for outcome evaluation at baseline (Prior to randomization, T_0_), 1-week post-intervention (T_1_), and 4-month post-intervention (T_2_):

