Socio-demographic and clinical data will be documented using a self-reported questionnaire, which covers participant profile (age, gender, marital status, educational level, religiosity, and financial status) and clinical data (onset time, PD staging, medication record, history of psychiatric disturbance, presence of comorbidity, history of rehabilitation service utilization). All these will be documented and considered as control variables in the data analysis.

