### Sample size estimation

To account for multiplicity, we consider 2.5% as the nominal level of significance by Bonferroni adjustment. Taking psychological distress as the primary outcome, a previous systematic review reported an effect size of 0.4 for meditation compared to cognitive behavioral therapy control [53], while our previous clinical trial reported an effect size of 0.6 for yoga compared to exercise control [39]. Taking a conservative approach, although the comparison is made to usual care, we anticipate a moderate effect size of 0.6 for the primary outcome. Using power analysis software Gpower 3.1, assuming an attrition rate of 20%, 168 participants will give a three-arm (56 each arm) RCT 80% power to detect an effect size of 0.6 at 2.5% level of significance.

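### The GEE, on its natural reading, estimates a difference in change from baseline; adjusting for the baseline score would be more precise, by an amount that depends on an unstated correlation

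*Protocol article*

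**What the plan says.** Under Study design and setting: "Repeated outcome measures will be assessed at three time points across the 6-month study period". Under Outcome measures these are "baseline (Prior to randomization, T_0_), 1-week post-intervention (T_1_), and 4-month post-intervention (T_2", so the first of the three is taken before any treatment is assigned.

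The Data analysis section specifies "Generalized estimating equations (GEE) with unstructured working covariance matrix at the individual level with repeated measurements", comparing all outcomes "between groups (i.e., time effect, group effect, group*time effect". It does not say in so many words whether T0 is a response or a covariate.

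On covariates it says: "All demographic and clinical variables (e.g. age, gender, religiosity, expectation on treatment credibility, etc.) will be accounted for in the analysis". The data meant to serve as control variables are set out at the end of the outcomes section: a socio-demographic profile and "clinical data (onset time, PD staging, medication record, history of psychiatric disturbance, presence of comorbidity, history of rehabilitation service utilization". The baseline score of the outcome being analysed appears in neither place. The section adds: "Both crude and adjusted GEE model analyses will be performed".

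The Sample size estimation section works from an effect size of 0.6, 20% attrition, 56 per arm (168 in all) and 80% power, where "we consider 2.5% as the nominal level of significance by Bonferroni adjustment". The Data analysis section makes all tests two-tailed at 0.025.

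**The concern.** If T0 is a response level, the group-by-time coefficient at T1 or T2 is the difference between arms in mean change from baseline. This estimator does not use the fact that randomisation makes the expected baseline means equal, and it fixes the slope on baseline at 1 instead of letting the data estimate it. A baseline-adjusted contrast has smaller variance for any correlation below 1 and uses data the trial already collects.

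The separately listed group effect is also open to misreading. With the interaction in the model and T0 as reference visit, it is the baseline difference, whose expectation is zero. If it is averaged over visits, it includes one visit at which no effect is possible. Neither is the treatment effect.

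What is at stake is precision on the HADS subscales, and clarity about which term carries the treatment comparison.

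**Working it through.** **Inputs from the article.** Effect 0.6; 56 per arm; attrition 20%, so 56 × 0.8 = 44.8 evaluable per arm; significance level 0.025; two-tailed tests; power 80%.

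**Assumptions.** The 0.6 is in SDs of the follow-up score; the SD is equal at baseline and follow-up; r, the correlation between the two, ranges over 0.3 to 0.85. The only related figures in the article are the HADS test-retest ICCs of 0.86 and 0.84 under Primary outcomes. They serve as a rough upper bound, because correlations over 8 and 24 weeks should be lower.

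**1. The plan's own figure.** A two-sample t-test with d = 0.6 and 80% power at one-sided 2.5% needs 45 per arm. 45/0.8 = 56.25, which matches the stated 56 per arm and 168 in total to rounding. At two-sided 0.025 it needs 55 per arm; 55/0.8 = 68.75, so 69 per arm or 207 in total. At 44.8 per arm and two-sided 0.025, a comparison of follow-up scores alone has 71% power. That mismatch is a separate point. The two-sided rule is used below because it governs the analysis.

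**2. What the planned contrast estimates.** An unstructured GEE with group, time and group-by-time on all three visits was fitted to simulated complete data. In one trial the T1 interaction coefficient was -0.7142 and the difference in mean change was -0.7142. Adding a patient-level covariate as a main effect left the estimate and its standard error (0.1802) unchanged. On complete data, therefore, an adjusted model of that form gives the same treatment contrast as the crude one.

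**3. Variance.** Per patient, in units of the squared SD:

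- change score: 2(1 - r)
- baseline-adjusted: 1 - r²
- ratio, adjusted to change: (1 - r²) / [2(1 - r)] = (1 + r)/2

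Across 3,000 simulated trials with r = 0.6 and 45 per arm, both estimators averaged -0.61 against a true -0.60. Their variances were 0.0352 (change) and 0.0290 (adjusted), a ratio of 0.82 against 0.80 in theory.

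**4. Power.** Noncentral t, 44.8 per arm, two-sided 0.025, with standardised effects 0.6/√[2(1 - r)] and 0.6/√(1 - r²):

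| r (assumed) | Variance ratio | Power, change score | Power, baseline-adjusted |
|---|---|---|---|
| 0.3 | 0.65 | 55% | 76% |
| 0.5 | 0.75 | 71% | 84% |
| 0.6 | 0.80 | 81% | 90% |
| 0.7 | 0.85 | 91% | 95% |
| 0.85 | 0.925 | above 99% | above 99% |

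The change-score analysis reaches 80% power at r of about 0.59; the adjusted analysis reaches it at about 0.42. Below r = 0.5 the change score is less precise than the follow-up score alone, since 2(1 - r) then exceeds 1.

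**The case against.** **The model is inferred.** The same three terms would fit a model of T1 and T2 with baseline as a covariate, and such detail is often left to an analysis plan. This stands as a caution. Even so, the article describes three repeated outcome assessments, analyses the repeated measurements without excluding T0, and lists covariates without the baseline score. Nothing in it points to baseline adjustment.

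**This is efficiency, not error.** The first hypothesis under Aims and hypothesis is about greater positive change, and a group-by-time contrast tests that directly and without bias. This stands in full. A reader might infer that the planned analysis is invalid or contradicts the hypothesis; the documents do not support that.

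**Power.** A reader might also infer that power is being thrown away in a trial already short of its target. That goes too far. The 71% at two-sided 0.025 belongs to a follow-up-only comparison, or to a change score at exactly r = 0.5. From r of about 0.59 upward, the change-score analysis meets the stated 80% under the assumptions used here. At r = 0.85 the variance saving is only 7.5%.

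**Dilution of the effect.** Averaging over three visits would turn an effect of 0.6 into (0 + 0.6 + 0.6)/3 = 0.4. This applies only if a visit-averaged group effect is used as the treatment test and the effect is equal at T1 and T2. The article lists the group effect as a term but does not make it the treatment test, so the 0.4 illustrates a misreading and is not a planned result.

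**Primary visit.** One might go on to make T1 the sole primary visit. The hypothesis covers both completion of the intervention and the 4-month follow-up, so that would narrow the objective and has nothing to do with precision.

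**Conclusion.** The point holds as one of precision and clarity. On the natural reading of the article, the treatment contrast is a difference in change from baseline: valid, but less efficient than a baseline-adjusted contrast, with the loss not recovered by the listed covariates if they enter as main effects. The variance saving from adjustment is (1 - r)/2: 35% at r = 0.3, 25% at 0.5, 15% at 0.7 and 7.5% at 0.85. Its practical value runs from material to negligible, because r is not given. It decides whether 80% power is reached only for r between about 0.42 and 0.59; below that, neither analysis reaches 80%.

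These figures assume T0 is a response level, equal SDs across visits, d = 0.6 in follow-up SD units, 44.8 evaluable patients per arm and two-sided 0.025. The group effect, however coded, should not be read as the treatment effect. The change is worth making; its absence would not invalidate the trial.

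**What to change.** State in the Data analysis section how baseline enters the model. Make T1 and T2 the response visits, include the T0 value of the same outcome as a covariate, and keep group, time and group-by-time. Alternatively, keep all three visits and constrain the T0 means to be equal across arms. Adding the T0 score as a main effect while T0 also remains an unconstrained response would not help, for the reason in step 2 of the working.

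Take each arm-versus-usual-care contrast at T1 and at T2 from this model as the treatment estimates, in place of an overall group effect. Which visit is primary is a separate decision for the sponsor.

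The cost is a change of wording made before outcome data are examined. No extra data or patients are needed.

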### Limitations

There are several potential limitations of the study. First, even though a range of recruitment strategies will be used to approach PD patients in various settings, the recruited participants may be more active in community engagement. This a possible source of selection bias which may limit the generalizability of the study findings to the less active group. Second, blinding the participants is inapplicable owing to the nature of the behavioral interventions, which may induce risks of bias in terms of performance, attrition, and evaluation. To minimize bias stemming from expectation, study participants will be blinded to study hypotheses and details of the study manuals. The information provided in the informed consent form followed the principle of equipoise by declaring uncertainty about the superiority of the treatment effect of both intervention arms. All participants will be reminded not to disclose their group status to the study assessor at any time point. Third, the validity of the study may be threatened by a high attrition as the intervention requires the participants to attend 8 face-to-face intervention sessions plus 3 assessment interviews, particularly during the coronavirus pandemic. To secure their attendance and ensure safety, appropriate public health control measures will be enforced in line with government regulations, such as mandatory mask-wearing and social distancing. If there is an unexpected lockdown, the research team will call upon an ad hoc meeting to discuss possible solutions, including, but not limited to, change of venue, schedule, and using a hybrid on-site/virtual delivery mode [61]. To reduce attrition among the control group, participants will receive the tested yoga intervention upon completion of the three assessment interviews over the 6-month study period. Finally, participants who have attended and completed the assessment interviews will receive HKD 50/50/100 cash incentive at the baseline, T1 and T2 follow-ups, respectively.

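### The one stated missing-data sensitivity analysis, complete versus non-complete cases, does not probe departures from missing at random on either reading of the sentence

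*Protocol article*

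**What the plan says.** The Data analysis section of the protocol article sets out the primary model as "Generalized estimating equations (GEE) with unstructured working covariance matrix at the individual level with repeated measurements", states that "An intention-to-treat principle will be adopted", and continues: "Multiple imputations will be used to account for missing data". Reporting is to follow a published guideline, which the article cites but does not describe. One sensitivity analysis for missing data follows: "Sensitivity analysis will be performed to compare the results between complete and non-complete cases". The article names no missingness assumption and no analysis in which missing values are allowed to differ from what the imputation model predicts.

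The article treats missing data as a real prospect. Sample size estimation has "assuming an attrition rate of 20%, 168 participants will give a three-arm (56 each arm) RCT 80% power to detect an effect size of 0.6". The Limitations section says that "the validity of the study may be threatened by a high attrition" and lists attrition among the biases that may arise because participants cannot be blinded.

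**The concern.** Standard multiple imputation usually rests on the assumption that data are missing at random: given what was observed, those with missing scores are like those without. The article states no other assumption. A useful sensitivity analysis moves that assumption and shows how far the result moves with it.

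The planned comparison does not do this. Whether someone is a complete case is settled after randomisation, and the Limitations section gives reasons why the causes may differ by arm. The active arms are asked to attend eight sessions, while controls are offered yoga after the last assessment in order to keep them in the study. Participants know their group, and the primary outcome, HADS, is self-reported. It is plausible that some active-arm participants leave because they did not benefit or did not tolerate the programme. If so, imputation from those who stayed would credit them with benefit they did not have, and the stated check would not show by how much the conclusion depends on this.

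**Working it through.** **1. The two readings side by side.**

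- Literal reading: results in complete cases against results in non-complete cases. Neither subset is a randomised comparison. At the visit that a person missed there is no observed HADS, so any result for non-complete cases at that visit comes from the imputation model itself. Someone who missed only the 24-week visit (T2) does have an observed 8-week score (T1), and a contrast at T1 is possible.
- Alternative reading: the complete-case result against the imputed result. Both are computed without any not-at-random scenario.

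Neither reading varies the assumption behind the imputation.

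**2. Does the size of the planned contrast signal whether imputation is biased?** A large-sample simulation (20,000 per arm, 10 repeats) set a true effect of −0.6 SD at T1 and T2, with 20% of T2 values missing in each arm. T2 was imputed by arm from a regression on baseline and T1. Two inputs are assumptions, not from the article: a correlation of 0.6 between visits, and an active-arm dropout slope of 1 on the log-odds scale per SD. Dropout depended on T1 under missing at random (MAR) and on the unseen T2 under missing not at random (MNAR). Under missing completely at random (MCAR) it depended on neither.

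| Mechanism | T1 effect, complete | T1 effect, T2 missing | T2 effect, complete cases | T2 effect, imputed | T2 effect, full data |
|---|---|---|---|---|---|
| MCAR | −0.599 | −0.601 | −0.595 | −0.595 | −0.595 |
| MAR | −0.774 | +0.098 | −0.707 | −0.602 | −0.600 |
| MNAR | −0.704 | −0.194 | −0.772 | −0.699 | −0.599 |

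- Literal reading, gap at T1: 0.774 + 0.098 = 0.872 under MAR, where the imputed result is right; 0.704 − 0.194 = 0.510 under MNAR, where it is off by 0.699 − 0.599 = 0.100.
- Alternative reading, gap at T2: 0.707 − 0.602 = 0.105 under MAR; 0.772 − 0.699 = 0.073 under MNAR.

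In these scenarios the gap is larger where imputation is valid. That ordering depends on the two assumed inputs. The general lesson is only that the size of the gap does not indicate whether the imputed result is biased.

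**3. How much could be at stake? An illustration.** Inputs from Sample size estimation: 56 per arm, 20% attrition, effect 0.6. From Data analysis: "All statistical tests will be two-tailed and statistical significance will be set at 0.025".

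- The plan's own figure: n per arm = 2(z for 1 − α/2 + z for 0.80)² / 0.6². At two-sided 0.025 this gives 53, and 53 / 0.8 rounds up to 67, so the stated 56 is not reproduced. At one-sided 0.025 it gives 44, and 44 / 0.8 = 55, close to 56. This is a separate matter; only the 56 and the 20% are used below.
- Observed per arm: 56 × 0.8 = 44.8, about 45.
- Effect if the 20% missing in an active arm had no benefit: 0.80 × 0.60 + 0.20 × 0 = 0.48.
- Smallest significant standardised difference with 45 per arm: t(0.9875; 88 df) × √(2/45) = 2.28 × 0.211 = 0.48.
- Delta adjustment: worsening the imputed active-arm values by δ SD moves the effect by 0.2δ. From 0.60 this gives 0.55 at δ = 0.25, 0.50 at δ = 0.5 and 0.40 at δ = 1.0.
- Tipping point for an observed 0.60: (0.60 − 0.48) / 0.2 = 0.6 SD.

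These are two-sample approximations. They ignore the extra variance from imputation and any gain from repeated measures or covariates.

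**The case against.** Several points on the other side have force.

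- The sentence follows directly on the one about imputation and may well mean complete-case against imputed results. On that reading the criticism that two post-randomisation groups are compared falls away. What stands is that neither estimate includes a not-at-random scenario.
- A reader might infer that the plan sets out to test the missing-at-random assumption and fails. The article claims no such test and never names the assumption. No analysis of observed data can test it, and the remedy below does not test it either; it shows how the result responds to departures.
- A reader might infer that everything reported for non-complete cases is imputed. That is too strong, since people missing only T2 have an observed T1 HADS.
- A reader might infer that departures from missing at random will never be examined. An unseen analysis plan may add such an analysis, and its absence from an article is not in itself a fault. The point here is about the analysis that the article does state.
- The planned contrast is not worthless. In the simulation it was essentially nil under MCAR and clearly non-zero otherwise, so it says something about departure from MCAR. That is a reason to keep it as a supplement.
- The cited reporting guideline was not available, so it counts neither for nor against the plan.

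**Conclusion.** The point holds as a low-cost improvement. The sensitivity analysis stated in the article does not, on either reading, probe departures from the assumption usual for standard multiple imputation, although the article plans for 20% attrition and itself acknowledges attrition bias.

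The size is illustrative. An effect of 0.60 becomes 0.48 if every missing active-arm participant had no benefit, which lies at about the edge of significance with 45 per arm. A reader might take this as an expected overstatement of one fifth. The article does not support that: the 20% is overall attrition, it can include people who finished the programme and missed only the last visit, and the Limitations section also links attrition to the assessment visits and the pandemic. Nor should the point be read as a loss of power caused by this analysis. A smaller true effect would reduce power whichever sensitivity analysis is chosen.

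**What to change.** In Data analysis, or in the analysis plan that supports it:

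1. Reword the sentence so that the complete-case analysis is defined as a supplementary comparison with the multiply imputed result.
2. Add a prespecified delta-adjusted multiple imputation by arm, on the primary model, for HADS anxiety and HADS depression. Shift the imputed active-arm scores towards worse values in stated steps.
3. Include a reference case in which missing active-arm values follow the usual-care distribution.
4. Report the shift at which the primary conclusion changes, so that readers can judge whether it is plausible.

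The cost is some wording and a few extra runs on imputations that are already planned, with no change to design, recruitment or data collection. The downside is a possibly less favourable statement of robustness.

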### Allocation concealment, assignment of interventions and blinding

After baseline assessment, participants will be randomly assigned into one of the three groups on a 1:1:1 basis using the method of permuted block, with random block sizes between 3, 6, and 9, and will be informed of their assigned group by an independent person not involved in the assessment. The allocation list will be computer-generated by an independent researcher and concealed from other researchers and participants until the time of assignment.

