#### Usual care group

The wait-list control group will continue with routine outpatient services (medication follow-up care with minimal health education on disease management/ drug care) and receive the tested yoga intervention [39] upon completion of the 6-month study period.

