#### Secondary outcomes

*Movement Disorder Society-Unified Parkinson’s Disease Rating Scale (MDS-UPDRS, Chinese)* will be used to measure PD-related motor and non-motor symptoms [43]. MDS-UPDRS consists of four parts, which examine: (i) non-motor experiences (cognitive impairment, hallucinations, depressed mood, anxious mood, apathy, and dopamine dysregulation), (ii) motor experiences of daily living, (iii) examination of motor symptoms (tremor, rigidity, bradykinesia, gait and postural instability), and (iv) motor complications (dyskinesia and motor fluctuations), respectively. Higher scores indicate greater disease severity. Cronbach’s alphas are 0.79–0.93 [44].

*Chinese Five-Facet Mindfulness Questionnaire (Short-form)* will be used to measure perceived mindfulness [45]. Using a 5-point Likert scale, this 20-item scale assess five mindfulness domains: observing, describing, acting with awareness, non-judgment of inner experience, and non-reaction to inner experience. Cronbach’s α is 0.82 [46].

*Parkinson’s Disease Questionnaire-8 (PDQ-8, Chinese)* will be used to measure PD-related HRQOL [47]. The 8-item scale yields a summary index score capturing disease-specific HRQOL regarding mobility, activities of daily living, emotional wellbeing, social support, communication, cognition, body discomfort and stigma. Higher scores indicate worse HRQOL. Cronbach’s α is 0.80 [48].

Plasma cortisol, IL-6 and TNF-α will be collected. To control for variations of cortisol levels over the circadian rhythm, all blood samples will be collected at 14:00 to 16:00, as cortisol level in this sub-period is relatively stable and highly correlated with mean 24-h cortisol level [49, 50].

The expectation on treatment credibility refers to the respondent’s expectation of the stress-reducing effect of the received intervention. A 4-item questionnaire will be used, rating: (i) reasonableness of treatment, (ii) opinion of the therapist, (iii) expectation for improvement, and (iv) likelihood to recommend the treatment to others, on a 10-point scale (higher scores indicating higher expectation) [51].

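### The adjusted model includes a treatment-credibility score defined by the intervention received; if a post-allocation value is used, the adjusted comparison with usual care can be distorted

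*Protocol article*

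**What the plan says.** The protocol article plans GEE models for all outcomes, both crude and adjusted, and does not say which is primary. On the covariates, Data analysis says: "All demographic and clinical variables (e.g. age, gender, religiosity, expectation on treatment credibility, etc.) will be accounted for in the analysis".

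Secondary outcomes gives the definition: "The expectation on treatment credibility refers to the respondent’s expectation of the stress-reducing effect of the received intervention". The four items are "i) reasonableness of treatment, (ii) opinion of the therapist, (iii) expectation for improvement, and (iv) likelihood to recommend the treatment to others". The paragraph that follows, on socio-demographic and clinical data, lists the control variables, and credibility is not among them. Data analysis alone makes it a covariate.

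On timing, Outcome measures says that "the following instruments will be used for outcome evaluation at baseline (Prior to randomization, T_0_), 1-week post-intervention (T_1_), and 4-month post-intervention (T_2"). Under Allocation concealment, assignment of interventions and blinding: "After baseline assessment, participants will be randomly assigned into one of the three groups on a 1:1:1 basis".

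On the comparator, Usual care group says: "The wait-list control group will continue with routine outpatient services". Controls are offered the yoga programme only once the 6-month study period has ended. Limitations states that participants cannot be blinded.

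**The concern.** A covariate in a randomised comparison should be fixed before allocation. This one is defined by reference to what the participant was given. Participants know their arm, and the primary outcome, HADS, is self-reported. Being offered yoga or meditation may raise expectation, and expectation may influence reported mood. Conditioning on such a variable removes the part of the effect that runs through it. It also links arm to any unmeasured cause shared by expectation and mood, so the adjusted contrast is no longer the randomised one.

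The score also lacks a common meaning across arms. During the study, controls have no mindfulness programme and no instructor to rate. A rating of usual care, or of a programme promised for later, is not on the same footing as a rating of a course in progress or completed.

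The comparison with usual care is the trial's first aim. With no primary model named, the affected estimate could become the headline result.

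**Working it through.** **Step 1. Which value can enter the model?** The protocol gives no figure on this point to reproduce, so the check begins with the text.

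- Definition (Secondary outcomes): expectation about the intervention received, with a therapist item. This points to a value taken after allocation.
- Schedule (Outcome measures): T0 before randomisation, then T1 and T2.
- Order of events (Allocation concealment): randomisation follows baseline assessment, so at T0 nobody has received an intervention or met its instructor.
- Model (Data analysis): no time point is given for the covariate.

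The definition and the T0 schedule do not fit together, and the analysis section does not choose between them.

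**Step 2. Size if a post-allocation value is used.** The setting is one active arm against control at a single time point, in a linear model, with benefit scored as positive.

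- Total effect 0.60 SD: Sample size estimation.
- a = shift in credibility caused by allocation, 0.5 or 1.0 SD: assumed.
- b = slope of outcome on credibility, 0.1, 0.2 or 0.3 SD per SD: assumed.
- Within-arm SD of credibility and of outcome = 1, and equal arms: assumed scaling.

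Formulas:

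- Adjusted effect = 0.60 − a × b.
- Squared correlation of arm and credibility = 0.25a² / (0.25a² + 1). This is 0.0625/1.0625 = 0.059 for a = 0.5 and 0.25/1.25 = 0.20 for a = 1.0.
- Variance inflation from collinearity = 1 / (1 − squared correlation) = 1.0625 and 1.25.
- Net variance factor = that inflation × (1 − b²), because the covariate also reduces residual variance.

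| a | b | Adjusted effect | Net variance factor |
|---|---|---|---|
| 0.5 | 0.1 | 0.60 − 0.05 = 0.55 | 1.0625 × 0.99 = 1.05 |
| 0.5 | 0.2 | 0.60 − 0.10 = 0.50 | 1.0625 × 0.96 = 1.02 |
| 0.5 | 0.3 | 0.60 − 0.15 = 0.45 | 1.0625 × 0.91 = 0.97 |
| 1.0 | 0.1 | 0.60 − 0.10 = 0.50 | 1.25 × 0.99 = 1.24 |
| 1.0 | 0.2 | 0.60 − 0.20 = 0.40 | 1.25 × 0.96 = 1.20 |
| 1.0 | 0.3 | 0.60 − 0.30 = 0.30 | 1.25 × 0.91 = 1.14 |

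A simulation with 400,000 records per scenario gave adjusted estimates from 0.550 down to 0.298 over this grid. The crude estimates stayed between 0.597 and 0.606.

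**Step 3. Adding a shared cause.** Suppose an unmeasured factor accounts for about 30% of the variance of both credibility and outcome (assumed). The coefficient of credibility becomes b + 0.3, and the adjusted effect becomes 0.60 − a(b + 0.3). For b from 0 to 0.3 this runs from 0.45 to 0.30 when a = 0.5, and from 0.30 to 0 when a = 1.0. The simulation agreed (0.448 to 0.299, and 0.296 to 0.004).

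**Step 4. Power on the Step 2 grid.** 56 × 0.8 = 44.8, so take 45 completers per arm, with a two-sided level of 0.025 and a normal approximation. The crude comparison has SE = √(2/45) = 0.211 and 0.60/0.211 − 2.241 = 0.61, which gives power of about 0.73. The adjusted comparison falls to between about 0.62 (a = 0.5, b = 0.1) and 0.18 (a = 1.0, b = 0.3). Only the drop matters here; the protocol's own sample-size figure is a separate question.

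**Step 5. When there is no bias.** With a value taken before randomisation, a = 0 and the adjusted estimate stays at about 0.60, with or without the shared cause. The estimate is also undisturbed if credibility has no relation to outcome once arm is taken into account.

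**The case against.** The strongest reply is that Outcome measures schedules the instruments at T0, before allocation, and that a true T0 score is a legitimate covariate that causes no bias. This stands as far as it goes: bias depends on a post-allocation value related to HADS being used. A reader might infer that the adjusted estimate is certain to be biased, and the document does not support that. Nor does the T0 reading rescue the text, since it conflicts with the definition and the same schedule also lists T1 and T2.

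The second reply is that a crude GEE is also planned and does not condition on credibility. That is correct and limits the damage. The risk remains because neither model is named as primary.

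Three other strong readings should not be drawn:

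- A reader might infer that the scale cannot be answered before randomisation. The reasonableness and expected-improvement items can be judged in advance, since intervention content is explained at consent. The therapist item is the one that clearly does not fit T0.
- A reader might infer that controls will have no score, and so will be dropped or given imputed ratings. The protocol does not say that controls skip the questionnaire and does not list the imputation variables. What the text supports is a lack of comparability.
- A reader might quote a flat 25% variance inflation. That figure ignores the residual variance the covariate removes. On the same assumptions with a = 1.0, the net inflation is 14% to 24%, and with a = 0.5 it is small or slightly negative.

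Finally, credibility counts as an outcome only through its position under the Secondary outcomes heading. The abstract and the aims do not list it.

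**Conclusion.** Wrong as written. The protocol commits to adjusting for a variable that its own definition ties to the intervention received, and its schedule and analysis sections do not settle which value is meant. Used as defined, the score can be affected by known allocation in an unblinded trial and is not comparable between the active arms and wait-list controls. It can then pull the adjusted effect towards zero: from 0.60 SD to about 0.55 to 0.30 on the assumed inputs, and lower if expectation and mood share unmeasured causes. Net variance inflation reaches about 24% at most on that grid.

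These sizes are illustrative, because the document gives neither the arm difference in credibility nor its relation to HADS. The conclusion about the covariate rule does not rest on them. It rests on the definition, the order of baseline assessment and allocation, and the absence of a named primary model. The crude GEE remains a valid randomised comparison as far as this point is concerned.

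**What to change.** In Data analysis, restrict the covariates of the arm-versus-usual-care models to variables measured before randomisation. Examples are baseline HADS (where it is not already one of the repeated outcomes) and the baseline values of the socio-demographic and clinical variables listed at the end of Secondary outcomes. Exclude any post-allocation credibility score from those models, and use it only descriptively or in comparing yoga with meditation.

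If a pre-randomisation expectancy score is intended as a covariate, reconcile Outcome measures, Secondary outcomes and Data analysis. Define it as expectation before allocation, leave out the therapist item, and state that only the T0 value enters the model.

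The cost is a sentence or two in the analysis section and a line in the assessment schedule. No patients or visits are added.
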